#### Study 4: study on effect of multimodal dementia prevention programme in community-dwelling elderly

This is a parallel exploratory intervention study, to explore the effects of multimodal interventions for slowing the process of cognitive decline. The target group were approximately 80 citizens over 70 years old who participated in a dementia prevention education programme which was held monthly by Kobe city in 2016. Individuals who agreed to participate in this study are randomly divided into two groups. Both groups undergo an intensive training programme (education, cognitive training and exercise) once a week for a total of 10 weeks and are monitored every 6 months for up to 30 months after recruitment. During the follow-up period, the intervention group receives a booster training once every 3 months, whereas the control group does not. The endpoints include changes in Mini Mental State Examination, CFI, EQ-5D, Five Cog, Timed Up & Go test, Physical Activity Scale for the Elderly and Geriatric Depression Scale. In the ANOVA between the three groups, effect size was set at 0.25, α=0.05 and power=0.80, the necessary data number will be approximately 50 persons for each group. Since this is a long-term longitudinal study, the number of subjects is set at a higher 100 persons, which is about double the necessary number (for statistical significance) as a cautionary measure for drop outs and missing data. The longitudinal change of the evaluation results in each group is analysed using repeated ANOVA and mixed effects model. The amount of change in the evaluation result between groups is compared by multiple comparison tests: the paired t-test or Wilcoxon test.

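### Study 4 foresees missing data but gives the randomised booster comparison to a paired t-test or Wilcoxon test on change, and not to the mixed model it already plans

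*Protocol article*

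**What the plan says.** All of this is in the protocol article, in the section on Study 4, except where noted.

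- **Design.** Participants are randomised to two groups and assessed every 6 months for up to 30 months. During follow-up, "the intervention group receives a booster training once every 3 months, whereas the control group does not".
- **Endpoint and size.** Table 1 gives MMSE as the primary outcome and a sample of 57.
- **Missing data.** The planned number is described as "about double the necessary number (for statistical significance) as a cautionary measure for drop outs and missing data". No dropout rate is given.
- **Change over time.** "The longitudinal change of the evaluation results in each group is analysed using repeated ANOVA and mixed effects model".
- **Comparison between groups.** "The amount of change in the evaluation result between groups is compared by multiple comparison tests: the paired t-test or Wilcoxon test".

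The article does not say which longitudinal method leads. It also does not say that the mixed model estimates the difference between groups.

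**The concern.** The randomised question is whether boosters change the course of MMSE. The method assigned to it uses only people who have both measurements. Someone who attends to month 24 and then withdraws adds nothing to a comparison of 30-month change, although four follow-up values are on file. Repeated ANOVA in its classical form is stricter still, since one missed visit removes the person. The mixed model, which uses all these records, is named only for change within each group.

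There is also a mismatch of design. A paired t-test, or a signed-rank Wilcoxon test, compares two measurements on the same people. The two randomised groups are different people, so a paired test cannot estimate the booster effect.

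Two things are at stake. Observed data are wasted in a small study. The people who remain may also be a selected set if loss depends on cognition and differs by arm. The arms do differ in contact, with extra 3-monthly training in one only, so unequal retention is plausible, though the article does not state it. A larger sample does not remove selection of this kind.

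**Working it through.** **1. The plan's own figure.** The plan states that "effect size was set at 0.25, α=0.05 and power=0.80" requires about 50 per group for three groups. Reading 0.25 as Cohen's f (an assumption), a one-way ANOVA with noncentrality N × f² needs 53 per group, and 50 per group gives power 0.780. So 50 is a rounded figure that is nearly reproduced. The text then says "the number of subjects is set at a higher 100 persons". This equals an allowance for 50% loss only if 50 is the total needed: 50 / (1 − 0.5) = 100. If 50 are needed in each of two groups, 2 × 50 = 100 leaves no reserve. No expected loss can be read from the doubling.

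**2. Who each named method can use.** Visits at months 6, 12, 18, 24 and 30 give 30 / 6 = 5 follow-up visits plus baseline.

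| Method | Assigned to | Records used |
|---|---|---|
| Repeated ANOVA (classical) | change in each group | people with all visits |
| Mixed effects model | change in each group | every attended visit |
| Paired t-test or Wilcoxon on change | comparison between groups | people with both measurements |

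The only method that uses partial records is not the one assigned to the randomised comparison.

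**3. How many people that could leave (illustration).** Let q be an assumed miss rate per visit, independent across visits. The share with no missed visit is (1 − q)^5.

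| q | (1 − q)^5 | of 57, all visits | 57 × (1 − q), one given visit |
|---|---|---|---|
| 5% | 0.774 | 44 | 54 |
| 10% | 0.590 | 34 | 51 |
| 13% | 0.498 | 28 | 50 |

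The third column is what classical repeated ANOVA would use. If misses are isolated, a comparison of 30-month change needs only the last visit and keeps the number in the fourth column. If q is instead the chance of leaving for good at each visit, it too falls to the third column. At 2% and 15% the third column would be about 52 and 25.

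**4. Bias and precision (simulation, all inputs assumed).** Inputs: 28 per arm, 6 visits, baseline mean 27, random-intercept SD 1.5, slope −0.6 per year (SD 0.6), residual SD 1.2, slope benefit 0 or 0.4 per year. The benefit gives a true 30-month difference of 0 or 0.4 × 2.5 = 1.0. The logit of dropout is −2.6 + k × (27 − last MMSE), with k = 0.45 in control and 0.15 in booster. About 35 completers remain.

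| True difference | Completers | Mixed model |
|---|---|---|
| 0 | −0.14 | about 0.00 |
| 1.0 | 0.89 | 1.03 |

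Over two sets of 300 simulated trials, the SD of the estimate (mixed model v completers) was 0.58 v 0.66 and 0.66 v 0.78 in one, and 0.65 v 0.79 and 0.69 v 0.83 in the other. The reductions are 1 − 0.58/0.66 = 12%, 1 − 0.66/0.78 = 15%, 1 − 0.65/0.79 = 18% and 1 − 0.69/0.83 = 17%. The second set fitted a straight line in time, which itself adds precision. A model with visit as a category would gain less.

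A separate simulation on an arbitrary scale used the same dropout rule in both arms, with about 48% completers and a true difference of 0.50. Completers gave 0.477 (Monte Carlo SE 0.011) and the mixed model 0.498 (SE 0.008).

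**The case against.** Three stronger readings are tempting, and the article supports none of them.

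- **That the study expects to lose half its data.** The larger number is only "as a cautionary measure for drop outs and missing data". That is a margin, not a forecast, and step 1 shows that it may not even be a margin.
- **That the plan is confined to completers.** The mixed model stands in the same sentence as repeated ANOVA, so it is not.
- **That the booster estimate will be badly biased.** The simulated bias of 0.11 to 0.14 points lies between 0.11/0.83 = 0.13 and 0.14/0.66 = 0.21 of the sampling SD. It rests on an assumed threefold difference between arms in how dropout depends on MMSE. In that simulation it runs against the booster, so it would not create a false benefit. Dropout there depends only on observed scores, which is the condition that favours a mixed model.

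It can also be said that the article does not state that incomplete records are dropped, and that ranking of analyses and rules for missing data are commonly left to a full protocol or SAP, which is not shown. That is fair: two unranked longitudinal methods would not by themselves be a finding. Study 4 is also labelled exploratory and its small sample is disclosed.

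What remains is something the article does state: the test it assigns to the comparison between groups. That test needs both measurements, cannot be paired across independent groups, and is weaker than a method already in the plan.

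**Conclusion.** The point holds in a limited form. Study 4 foresees missing data over up to five follow-up visits, yet assigns no analysis of all available data to the randomised booster comparison. One of the two tests it does assign, the paired t-test, does not suit independent groups. Repeated ANOVA adds a second longitudinal result on a possibly smaller set of people.

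The more certain cost is precision. Under the assumed miss rates of 5% to 13%, between 44 and 28 of the 57 would have complete follow-up, and the simulated SD of the mixed-model estimate was about 12% to 18% smaller than that of completers. Bias is probably modest, near 0.1 MMSE points under the dropout assumed, and could be nil or larger under other patterns. The mixed model is valid if missingness depends on observed values; it does not cure loss that depends on unseen decline.

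Severity is minor to moderate. The study is exploratory, but its results are meant to guide later studies, and the booster difference is the result they would carry forward.

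**What to change.** Replace the two analysis sentences for Study 4 with one main analysis of the difference between groups:

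- a mixed-effects model with arm, visit, arm-by-visit and baseline value, applied to MMSE and to each secondary scale;
- all randomised participants in the arm assigned, with every visit attended;
- the visit at which the difference is read, for instance the last planned one at month 30.

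Drop repeated ANOVA and the paired t-test or Wilcoxon comparison. If a completer analysis is wanted, keep it as a sensitivity analysis, with a test for independent groups. Report dropout by arm and visit. Include the number with no follow-up visit, since a model that uses baseline as a covariate gains nothing from them.

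The cost is wording only. The model is already planned, the visits already exist, and no extra participants or assessments are needed.

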### Outline of studies included in the project

The four studies are briefly explained below and summarised in table 1.

**Table 1 T1:** Summary of studies

	Study 1	Study 2	Study 3	Study 4
Target population for recruitment	General Population (80 000)	Citizens with Possible Cognitive Decline (4131)	‘Frail Check’ Participants (4800)	Brain health school programme participants (80)
Sample population	50 155	2385	2705	57
Baseline evaluation	KCL	CFI, EQ-5D, GDS	CFI, EQ-5D, General Frailty Measures	MMSE, EQ-5D CFI, GDS, etc
Primary outcome	LTC Need	LTC Need	LTC Need	MMSE
Secondary outcome	LTC Need Level	CFI, EQ-5D	LTC Need Level	EQ-5D, CFI, Five Cog, etc
Intervention	None	None	None	Intensive Cognitive Training
Study period	4–5 years	2 years	2 years	30 months

CFI, Cognitive Function Instrument; GDS, Geriatric Depression Scale; KCL, Kihon Check List; LTC, long-term care; MMSE, Mini Mental State Examination.

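### Study 4's only stated between-group comparison tests raw change, which cannot adjust for the baseline scores the study collects; the contrast is unbiased but gives up precision of uncertain size

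*Protocol article*

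**What the plan says.** The Study 4 section of the protocol article describes a randomised comparison: "Individuals who agreed to participate in this study are randomly divided into two groups". Both groups receive the same 10-week programme, and only the intervention group then receives quarterly boosters. Monitoring is every 6 months for up to 30 months.

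Two sentences describe the analysis:

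- Over time: "The longitudinal change of the evaluation results in each group is analysed using repeated ANOVA and mixed effects model".
- Between groups: "The amount of change in the evaluation result between groups is compared by multiple comparison tests: the paired t-test or Wilcoxon test".

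Table 1 gives the Study 4 baseline evaluation as "MMSE, EQ-5D CFI, GDS, etc". It lists MMSE as the primary outcome, EQ-5D and CFI among the secondary outcomes, and a sample of 57. The sample-size text uses "effect size was set at 0.25, α=0.05 and power=0.80" for a three-group ANOVA. The article gives no SD, no correlation between baseline and follow-up scores, and no dropout rate.

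**The concern.** Subtracting the baseline is not the same as adjusting for it. A change score fixes the coefficient of follow-up on baseline at 1. When the true slope is lower, the change score carries extra baseline noise and is negatively correlated with baseline. Adjustment estimates that slope and removes the noise.

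The sentence on comparing the groups names a t-test or a Wilcoxon test, and neither accepts a covariate. As written, it therefore rules out using the baseline scores. Study 4 is the project's only randomised comparison, and its sample of 57 is well below the 100 planned. The form of the analysis is one of the few ways left to gain precision without recruiting more people.

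A separate fault lies in the same sentence: a paired test cannot compare two independent groups. Correcting only that, by naming a two-sample test on change, would leave the present point untouched.

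**Working it through.** **Plan's own figure.** The sample-size sentence begins "In the ANOVA between the three groups" and concludes that "the necessary data number will be approximately 50 persons for each group". A three-group one-way ANOVA with Cohen's f = 0.25, alpha 0.05 and power 0.80 needs 52.4, so 53 per group. At 50 per group, power is 78.0%. The stated 50 is thus a loose rounding and no error in itself, but it describes three groups and the design has two.

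**Inputs for the check**

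- From Table 1: N = 57. The allocation ratio is not stated; 1:1 is assumed, giving 57/2 = 28.5 per arm.
- From the Study 4 section: effect size 0.25, read as f, so d = 2f = 0.5 for two equal groups. This reading is an inference. It is applied to the SD of change.
- Assumed: two-sided alpha 0.05, an independent-groups test at one time point, no dropout, and rho from 0.3 to 0.9.

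**Variances.** Let b and s be the baseline and follow-up SDs.

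- Change: b² + s² − 2·rho·b·s
- Baseline-adjusted residual: s²(1 − rho²)
- Difference (change minus adjusted): (b − rho·s)², which is never negative

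With b = s the ratio of adjusted to change variance is (1 − rho²)/[2(1 − rho)] = (1 + rho)/2. At rho 0.5 it is 0.75, and 1/0.75 = 1.33, equivalent to about one third more participants.

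**Power.** Noncentral t with d = 0.5 (55 df) for change, and d = 0.5/√ratio (54 df) for the adjusted analysis. The change analysis has 45.8% power throughout.

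| rho | ratio, s = b | adjusted power | gain | ratio, s = 1.2b | adjusted power | gain |
|---|---|---|---|---|---|---|
| 0.3 | 0.65 | 63.3% | 17.5 | 0.762 | 56.5% | 10.7 |
| 0.5 | 0.75 | 57.2% | 11.4 | 0.871 | 51.1% | 5.3 |
| 0.7 | 0.85 | 52.0% | 6.2 | 0.966 | 47.0% | 1.3 |
| 0.8 | 0.90 | 49.8% | 4.0 | 0.997 | 45.9% | 0.1 |
| 0.9 | 0.95 | 47.7% | 1.9 | 0.977 | 46.6% | 0.8 |

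Gains are in percentage points. Worked example at rho 0.5 with s = 1.2b: change variance 1 + 1.44 − 1.2 = 1.24; adjusted variance 1.44 × 0.75 = 1.08; ratio 1.08/1.24 = 0.871.

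A 10,000-run simulation at rho 0.5 with equal variances gave 46.0% and 56.8%. If d = 0.5 is instead taken on the SD of the raw score, with equal variances, the gains are 14.6, 11.4, 7.0, 3.6 and 0.3 points at rho 0.3, 0.5, 0.7, 0.8 and 0.9.

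**Bias and imbalance.** In the simulation the mean change contrast was 0.497 against a true 0.500, so it is unbiased over randomisations. Given an observed baseline difference, with equal variances, the estimate shifts by −(1 − rho) times that difference. One standard error of the baseline difference is √(2/28.5) = 0.265 SD. The shift is then 0.5 × 0.265 = 0.13 SD at rho 0.5 and 0.2 × 0.265 = 0.05 SD at rho 0.8.

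**The case against.** The strongest objections, and what stands of each:

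- **Bias.** A reader might infer that chance baseline imbalance biases the booster effect. The documents do not support that: allocation is random, so the change contrast is unbiased overall. The conditional shift is chance error that the variance ratio already counts, and is not a second harm to add to the power loss. This objection stands in full.
- **Size.** A reader might also take 11 points as a fact about this study. It rests on an assumed rho, on equal variances and on d inferred from a three-group calculation. If scores spread over follow-up, the gain falls sharply. This also stands, so only a range can be given.
- **The mixed model.** One is already planned, and its covariates may be set out in a fuller document that is not shown. That no covariate is named for it is not held against the plan. But the article assigns that model to change within each group and gives the between-group comparison to tests that take no covariate.
- **Exploratory status.** Study 4 is described as highly exploratory, and a change-score analysis is valid. That limits how much is at stake. It does not remove the case for a more precise estimate where the aim is to guide later studies.
- **The comparator.** The 45.8% is for an unpaired test that the article does not name, because the paired test it does name cannot make this comparison. This is true and is listed among the assumptions.

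**Conclusion.** The point holds as one of precision. The stated between-group method excludes baseline adjustment although the baseline scores are collected. Under a linear model, adjustment loses nothing beyond the degrees of freedom it uses. The direction is firm; the size is not.

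With d = 0.5 on the SD of change, an independent-groups test and all 57 analysed, the gain runs from about 17 points at rho 0.3 to about 2 at rho 0.9 with equal variances. It is about 5 points at rho 0.5, and close to nothing at rho 0.8, if the follow-up SD is 1.2 times the baseline SD. In none of these settings does adjusted power reach 80%; the highest is 63.3%. The analysis is valid as a change-score comparison but is worth improving.

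**What to change.** In the Study 4 section, replace the sentence on comparing the amount of change between groups with:

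> The between-group (booster vs no booster) difference in each endpoint is estimated by ANCOVA on the follow-up score, or by a mixed model for repeated measures with group, visit and group-by-visit, adjusting for the baseline value of the same endpoint.

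Unadjusted mean changes can stay as descriptive summaries. The same edit removes the paired test from the between-group comparison.

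No new data are needed and a mixed model is already planned. A single baseline term costs one degree of freedom. A baseline-by-visit term costs more: with six-monthly visits to 30 months there are up to 30/6 = 5 follow-ups, so up to about five baseline coefficients on 57 people before dropout. The approximately linear relation with baseline should be checked, given a possible MMSE ceiling.

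### Study 4 names a paired t-test, or a Wilcoxon test of unstated type, for comparing change between two independently randomised groups

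*Protocol article*

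**What the plan says.** All of this is in the protocol article, in the section on Study 4, unless stated otherwise.

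- Design: "This is a parallel exploratory intervention study, to explore the effects of multimodal interventions for slowing the process of cognitive decline".
- Allocation: "Individuals who agreed to participate in this study are randomly divided into two groups". No matching, pairing or crossover is described, and no allocation ratio is given.
- Contrast: both groups receive the same weekly programme for 10 weeks. Then "the intervention group receives a booster training once every 3 months, whereas the control group does not". Monitoring is every 6 months for up to 30 months.
- Longitudinal analysis: "The longitudinal change of the evaluation results in each group is analysed using repeated ANOVA and mixed effects model".
- Between-group analysis: "The amount of change in the evaluation result between groups is compared by multiple comparison tests: the paired t-test or Wilcoxon test".
- Outcomes: seven measures are listed as endpoints. Table 1 gives the Mini Mental State Examination (MMSE) as the primary outcome of Study 4 and a sample of 57.

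**The concern.** The only randomised question in Study 4 is whether booster sessions alter the course of the scores compared with no boosters. The sentence that addresses it names a test for linked observations, while participants in the two arms are not linked.

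The familiar use of a paired t-test on such data is baseline against follow-up inside one arm. Here that change contains the effect of the shared 10-week programme, practice from repeated testing, and ageing. All three act in both arms and none of them is the booster effect. A reader who then sees a significant change in one arm and none in the other may take this for a booster effect, which it does not establish.

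The multiple comparison label adds to the confusion. It suggests that multiplicity over the listed endpoints is handled, but neither named test adjusts for it.

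**Working it through.** **1. The plan's own figure.** The only number tied to the Study 4 analysis is the sample size: "In the ANOVA between the three groups, effect size was set at 0.25, α=0.05 and power=0.80", giving "the necessary data number will be approximately 50 persons for each group". One-way ANOVA with f = 0.25, three groups, α = 0.05 and power 0.80 needs 53 per group by the noncentral F distribution (power 0.780 at 50), or 52 by the large-sample chi-square version. That is close to the stated approximate 50. The calculation is for a comparison between separate groups, so it too presupposes independent groups. That it counts three groups where two are described is a separate matter, and the point here does not depend on it.

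**2. What each reading of the paired test measures.** Let D be a participant's change from baseline, c the mean change common to both arms, and b the added effect of the booster.

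- Within the intervention arm, the mean of D estimates c + b. Within the control arm it estimates c. Each paired test asks whether its own mean is zero, and neither asks whether b is zero.
- Between independent arms, mean D (intervention) − mean D (control) estimates b, with standard error s·√(1/n₁ + 1/n₂).
- Across arms with arbitrary pairs, the mean difference still estimates b, but the p-value depends on who is paired with whom, and unequal arms lose participants.

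**3. Size of the problem under the within-arm reading.** The documents give no SD, expected change or arm sizes, so these are assumptions: normal change scores with SD 1; arms of 29 and 28 (the 57 in Table 1 split as evenly as possible) or 50 and 50; b = 0; c = 0, 0.3 or 0.5 SD; two-sided 0.05; 20,000 simulated trials.

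If p₁ and p₂ are the chances of significance in each arm, then P(intervention arm only) = p₁(1 − p₂) and P(arms disagree) = p₁(1 − p₂) + p₂(1 − p₁).

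| Arms | c (SD) | p₁ | p₂ | Intervention arm only | Arms disagree | Independent t-test rejects |
|---|---|---|---|---|---|---|
| 29/28 | 0 | 0.051 | 0.050 | 0.048 | 0.096 | 0.049 |
| 29/28 | 0.3 | 0.350 | 0.331 | 0.234 | 0.449 | 0.047 |
| 29/28 | 0.5 | 0.740 | 0.725 | 0.201 | 0.388 | 0.051 |
| 50/50 | 0.3 | 0.550 | 0.549 | 0.249 | 0.496 | 0.048 |
| 50/50 | 0.5 | 0.933 | 0.937 | 0.059 | 0.121 | 0.049 |

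Check for 29/28 at 0.3 SD: 0.350 × (1 − 0.331) = 0.234. Adding 0.331 × (1 − 0.350) = 0.215 gives 0.449, as simulated. The last column counts rejections in either direction.

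**4. The arbitrary-pairing reading.** With 28 arbitrary pairs (one participant left out) and b = 0, the paired test rejects in 4.9 to 5.2% of trials. With a true difference of 0.5 SD, its power is 0.44 against 0.46 for the independent t-test. Type I error is therefore kept and little power is lost, but the result rests on a pairing that has no basis in the design.

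**5. Whether another sentence supplies the comparison.** The repeated ANOVA and mixed model are assigned to change in each group. A mixed model with a group-by-time term would give the contrast, but the text does not give it that task. The between-group question is assigned to the paired t-test or Wilcoxon test.

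**The case against.** Several objections have force.

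- **Wilcoxon is not necessarily wrong.** A reader might infer that both named tests are invalid. The document does not support that: the rank-sum form suits independent groups. Beside a paired t-test the name reads more naturally as signed-rank, but for this half the fault is ambiguity.
- **The contrast is not shown to be absent.** A reader might infer that nothing in the plan can estimate the booster effect. The sentence does state a between-group aim, a mixed model is planned, and an article may leave model terms to a fuller document. Arbitrary pairing would also still yield a mean difference. What stands is that the article itself fixes a test for this comparison, and the test it fixes does not match the design.
- **No decision rule is stated.** A reader might take 20 to 23% as the plan's false-positive rate. Nowhere does the protocol say that an effect will be declared because one arm is significant and the other is not. The figures illustrate a risk, and they move with the assumed common change and arm size.
- **The study is exploratory.** The Abstract, the Background and the section on strengths and weaknesses all say so, and the other three studies do not use this test. This lowers the consequence but does not make the test correct. The stated purpose is to find clues for later studies, and a spurious booster signal would misdirect them.

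**Conclusion.** The point holds in a limited form. The paired t-test is the wrong test for comparing change between two unmatched randomised groups, the type of Wilcoxon test is not stated, and the multiple comparison label is incorrect. Since the repeated ANOVA and mixed model are described only within groups, the article names no clearly valid between-group analysis.

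If within-arm tests were used for inference with no true difference, significance in the intervention arm only would occur in about 20 to 23% of trials for arms of 29 and 28 and a common change of 0.3 to 0.5 SD. Over all the scenarios tabulated the range is about 5 to 25%. The independent t-test stays near 5%. These sizes rest on assumed splits, common changes and normality; the mismatch between test and design rests on the text alone. Severity is moderate because the study is declared exploratory and no confirmatory claim depends on it.

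**What to change.** Replace the sentence on between-group comparison with one of the following:

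- the group-by-time contrast from the mixed effects model already planned, adjusted for baseline score, reported with a 95% CI; or
- an independent-samples t-test on change, with the Wilcoxon rank-sum test (stated as such, not signed-rank) as the non-parametric alternative.

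Name MMSE as the main outcome for this comparison, in line with Table 1. The Abstract gives long-term care certification as the primary outcome of all studies, so the authors should confirm that Table 1 governs Study 4. Keep paired tests only for describing change within an arm, and drop the multiple comparison label.

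The cost is a change of wording. The comparison uses the same baseline and six-monthly scores that the study already plans to collect.
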